### Study flow

After enrolment, both interventions will preferably be performed during the same hospitalization. Patients will be followed for a minimum of 24 months after randomization. Regular outpatient visits will be performed at 1, 6, 12, and every 6 months thereafter. Patients will be followed up for the occurrence of the primary and secondary endpoints, echocardiographic examination, and device interrogations. Symptoms will be evaluated with NYHA and EHRA‐AF scores, while quality of life will be assessed using the KCCQ. Data regarding HF hospitalizations and cardiovascular deaths will be collected continuously as presented in *Table* *3*.

**Table 3 ejhf70013-tbl-0003:** Time and events table of the CONDUCT‐AF trial

	Enrolment (−7 to −1 days)	Implant (day 0)	Discharge	FU 1 (1 M ± 7 days)	FU 2 (6 M ± 10 days)	FU 3 (12 M ± 15 days)	FU 4 (18 M ± 30 days)	FU 5 (24 M ± 30 days)
Eligibility check	x							
Informed consent	x							
Demographics	x							
Comorbidities	x							
Medication	x			x	x	x	x	x
Randomization	x							
Device implantation and AVNA		x						
ECHO	x		x		x			
12‐lead ECG	x		x	x	x	x	x	x
EHRA‐AF score	x				x			
NYHA class	x				x			
KCCQ score	x				x			
6MWT	x				x			
Lab testing	x				x			
Review clinical outcome events^a^				x	x	x	x	x
Device interrogation				x	x	x	x	x

6MWT, 6‐min walk test; AVNA, atrioventricular node ablation; ECG, electrocardiogram; ECHO, echocardiographic examination; EHRA‐AF, European Heart Rhythm Association score of atrial fibrillation; FU, follow‐up; KCCQ, Kansas City Cardiomyopathy Questionnaire; M, months; NYHA, New York Heart Association.

^a^
Hospitalization for worsening heart failure, hospitalization for ventricular tachycardia/implantable cardioverter‐defibrillator shock, need for reintervention, death.

### Trial interventions

Device implantation will always precede AVNA. Crossover between pacing modalities will be permitted in cases of unfeasible LBBAP implantation (due to high threshold, failure to penetrate the septum, or unmet criteria for conduction system capture) or failed BVP implantation due to anatomical constraints that preclude the LV lead from being placed in an acceptable position. The additional defibrillator lead will be implanted at the discretion of the implanting physician as indicated in the guidelines.^25^

#### Biventricular pacing

Implantation of the biventricular device will be performed using standard techniques. The RV lead will be positioned in the RV apex or septum, while the LV lead will be delivered to the most appropriate coronary sinus tributary, preferably the posterolateral or lateral vein. Optimal V‐V delay and appropriate LV vector in a multipolar LV lead will be selected after the procedure to achieve the narrowest possible QRS complex.^17^

#### Conduction system pacing

Left bundle branch area pacing will be the preferred pacing technique in patients randomized to the CSP group. The implantation technique has been described elsewhere.^24^ In brief, after localizing the His bundle area (fluoroscopically or determined with intracardiac signal), the LBBAP lead will be positioned approximately 1–1.5 cm distally to the His bundle position in the RV septum. Before screwing the lead into the interventricular septum, the suitable position will be confirmed by fluoroscopic features and adequate paced QRS morphology (‘w’ pattern in lead V1, polarity discordance of leads II and III). Lead progression into the interventricular septum will be monitored using progressive change of paced QRS morphology, fixation beats, local endocardial electrogram, impedance, and current of injury. Confirmation of conduction system capture will be desired.^26^ Given that the pacing parameters with LBBAP are typically low and stable, a backup RV lead will not be mandatory but can be implanted at the discretion of the operator.

If LBBAP is unobtainable, HBP implantation will be attempted. The procedural steps for delivering HBP were previously reported.^20^, ^22^ In short, the same leads and dedicated delivery sheaths as with LBBAP will be used for HBP. His bundle potential mapping will be performed in a unipolar setting using the electrophysiological system at a sweep speed of 100 mm/s and under fluoroscopic guidance. Distal His bundle potential with large ventricular signal and small atrial signal (ventricular to atrial electrogram ratio >3:1) will be targeted before the pacing lead will be screwed into position. An acute HBP threshold ≤2 V at 1 ms will be considered acceptable. The additional backup lead will be mandatory for all patients receiving HBP devices.

#### Atrioventricular node ablation

Atrioventricular node ablation will be performed following pacemaker implantation (preferably during the same hospitalization), which will temporarily be set to 40 bpm for the duration of the procedure. After femoral vein access is obtained, the ablation catheter will be positioned to the presumed area of the atrioventricular node in the mid‐septum under fluoroscopy and according to the intracardiac electrograms. Ablation will be performed in a temperature‐controlled (40 W, non‐irrigated tip catheter, up to 60 s) or power‐controlled mode (40 W, irrigated tip catheter, up to 60 s). AVNA will be considered successful after clearly documented presence of a complete atrioventricular block that will persist after a mandatory 20‐min waiting period. Each pacemaker will be tested after the procedure and at every follow‐up at a lower pacing rate (30 bpm) to check for any relevant escape ventricular rhythm. Any acute change in device lead position or pacing threshold following AVNA will be monitored. After AVNA, the pacemaker will be initially programmed to operate in VVI mode at 90 bpm base rate. At 1‐month follow‐up, the base rate will be decreased to 70 bpm.

### Echocardiographic examination

An echocardiographic assessment will be obtained before enrolment, after AVNA, and at the 6‐month follow‐up visit. All participating centres will receive a detailed echocardiographic protocol. Transthoracic echocardiographic images will be obtained according to guidelines following the European Association of Cardiovascular Imaging (EACVI) recommendations.^27^ Participating sites will follow a standardized imaging protocol, including specific image acquisition views in two‐dimensional imaging, to ensure uniformity across all study participants. All videos should include five cardiac cycles. During echocardiographic examination heart rhythm and heart rate will be continuously monitored and recorded. As stated previously, at the 1‐month follow‐up, the base rate will be decreased to 70 bpm, and the echocardiographic examination at the 6‐month follow‐up will be performed at the uniform base rate. Images will be acquired using commercially available ultrasound systems and stored in Digital Imaging and Communications in Medicine (DICOM) format. All echocardiographic studies will be anonymized and securely transferred to the independent Core Laboratory (University Medical Centre Maribor, Maribor, Slovenia), which is blinded to treatment allocation. The core laboratory will provide standardized echocardiographic assessments, ensuring consistency in measurement and interpretation. Measurements of LV volumes and LVEF will be performed using Simpson's method of disk summation. To reduce inter‐cycle variability, relevant echocardiographic measurements will be averaged over five subsequent cardiac cycles.

### Study timeline

Recruitment began in July 2023 and is expected to be completed by the end of 2025. Follow‐up is expected to be concluded by the end of 2027. The expected total study duration will be approximately 4.5 years, composed of 2.5 years of patient enrolment and 2 years of study follow‐up. The short‐term analysis of the primary outcome is expected in 2026, while secondary outcomes will be reported by the end of 2027.

### Sample size and statistical considerations

The study is designed to test the two‐sided hypothesis, at a type I error level of 0.05, that participants assigned to the CSP group would achieve a non‐inferior improvement of LVEF compared to the participants assigned to the BVP group, with the non‐inferiority margin of 5%. Additionally, an allowable absolute difference of 5% in echo measurement of LVEF with Simpson biplane was set to cover the intraobserver variability. To estimate the sample size and study power, we used the linear mixed model. Although there is an absence of robust estimation from the literature, according to the non‐randomized study, the predicted mean change of LVEF in the population would be +12% in the CSP group and −1% in the BVP group.^24^ According to available data, the maximum standard deviation of measured LVEF in the CSP group was 13% and 15% in the BVP group.^21^, ^23^, ^24^ Therefore, the LVEF change in the CSP group would be distributed in the population as *N* (12, 13^2^) and in the BVP group as *N* (−1, 15^2^). Based on these assumptions, we calculated that the necessary sample size would be 70 participants (35 patients in each group) to achieve a power of 0.9996 and yield a statistically significant result. The dropout rate was assumed at 15% due to study withdrawal or loss to follow‐up. Consequently, the target patient number was set as 82 participants.

Acknowledging limited data available in the literature, we conducted several sample size simulations to address the robustness of our assumptions across a plausible range of ejection fraction responses after both pacing modalities. Even in a more conservative scenario where the CSP group follows a *N* (7, 13^2^) and BVP group a *N* (0, 15^2^) distribution, the calculated power remains above 80%. The ALTERNATIVE‐AF trial showed improvement in LVEF in both pacing modalities with only 5% absolute difference in favour of CSP.^28^ Even in this scenario (CSP mean ejection fraction change: +12%, BVP mean ejection fraction change: +7%), the calculated power would remain >95% to demonstrate the non‐inferiority.

Data management will be performed using the Research Electronic Data Capture – REDCap (Vanderbilt, Nashville, TN, USA) and statistical analyses using the R programming language. The trial will follow an intention‐to‐treat analysis approach.

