### Study objectives and endpoints

The CONDUCT‐AF study aims to confirm the non‐inferiority of CSP versus BVP in echocardiographic and clinical outcomes, during a 24‐month follow‐up in HF patients with symptomatic AF and narrow QRS scheduled for AVNA. The study primary endpoint is the LVEF change from baseline to 6 months. Changes in indexed LV end‐diastolic and end‐systolic volumes from baseline to 6 months will be reported as secondary endpoints. These will also include the composite of worsening HF or cardiovascular death and its individual components. Worsening HF was defined as an episode of HF that requires unplanned medical attention with an increase in diuretic dose or intravenous diuretic therapy or HF hospitalization. The total number of HF hospitalizations will be reported. Clinical parameters, including changes in functional NYHA class, NT‐proBNP level, quality of life, and 6MWT distance, will be assessed after 6 months. Additional secondary endpoints are safety endpoints related to procedure success and adverse events. A detailed list of pre‐specified study endpoints is provided in *Table* *2*.

**Table 2 ejhf70013-tbl-0002:** Primary and secondary endpoints of the study

Outcomes	Time frame
Primary outcome measure	
Change in left ventricular ejection fraction	Baseline and 6 M
Secondary outcome measures	
Time to the first occurrence of worsening HF or cardiovascular death	At least 24 M
Time to the first occurrence of worsening HF	At least 24 M
Time to cardiovascular death	At least 24 M
Total number of HF hospitalizations	At least 24 M
Change in indexed LV end‐diastolic and end‐systolic volumes	Baseline and 6 M
Improvement in clinical parameters (NYHA class, EHRA‐AF, KCCQ score)	Baseline and 6 M
Change in the 6‐min walk test	Baseline and 6 M
Laboratory parameters – NT‐proBNP	Baseline and 6 M
Procedural‐related characteristics (total procedure and fluoroscopy time)	Peri‐procedural
Procedure‐associated adverse events	30 days after the procedure
Need for procedural reintervention	At least 24 M
ECG parameters (QRS duration)	Baseline and after the procedure
Pacing parameters (capture threshold, lead impedance)	At least 24 M
Number of detected sustained VT/VF	At least 24 M

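### The robustness claim rests only on scenarios in which CSP beats BVP by 5 to 13 points; at equality, non-inferiority power is about 32% at the plan's SDs, and the article states no superiority step

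*Protocol article*

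**What the plan says.** The section on sample size and statistical considerations sets a non-inferiority hypothesis for LVEF change, with a margin of 5% and "at a type I error level of 0.05", two-sided. For the base case, "the predicted mean change of LVEF in the population would be +12% in the CSP group", against -1% with BVP. For variability, "the maximum standard deviation of measured LVEF in the CSP group was 13% and 15% in the BVP group". It continues: "Based on these assumptions, we calculated that the necessary sample size would be 70 participants", 35 per arm, with power 0.9996, raised to 82 for 15% dropout.

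On robustness, the article says that "we conducted several sample size simulations to address the robustness of our assumptions across a plausible range of ejection fraction responses". Two further scenarios are printed: +7 against 0, with power above 80%, and +12 against +7, with power above 95%.

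The stated aim is non-inferiority throughout. The abstract, the limitations section and the objectives section agree on this, the last speaking of non-inferiority "of CSP versus BVP in echocardiographic and clinical outcomes". Superiority appears only under adverse events, as BVP over CSP, as a ground for early termination. No test of CSP superiority is stated.

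**The concern.** The natural reference case for a question of whether one treatment is not worse by more than 5 points is that the two treatments do equally well. The printed differences are +13, +7 and +5, all in favour of CSP, so the case that most tests a non-inferiority design is not among them. A reader told that the design is robust would not learn that it needs CSP to be clearly better.

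If the true difference is near zero, the likely result is an inconclusive trial: an interval that reaches below -5, which could be misread as a failure of CSP. The +13 comes from a non-randomized study, and the article concedes that robust estimates are lacking. Crossover is permitted and the analysis is by intention to treat, so any crossover would tend to pull the observed difference towards zero.

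Conversely, if CSP is as much better as the base case assumes, the article gives no planned route from non-inferiority to a superiority statement.

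**Working it through.** **Inputs** (all from the sample size section): margin 5, read as absolute LVEF points; SDs 13 (CSP) and 15 (BVP); two-sided 0.05, so z = 1.960 for the non-inferiority bound; 35 evaluable per arm. With no dropout at all, 82/2 = 41 per arm.

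**Formula.** SE = sqrt((13² + 15²)/n) = sqrt(394/n), which is 3.355 at n = 35 and 3.100 at n = 41. Non-inferiority power = Φ((d + 5)/SE − 1.960), where d is the true difference, CSP minus BVP.

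**The plan's own figure first.** d = 12 − (−1) = 13: Φ(18/3.355 − 1.960) = 0.9997, or 0.9996 with a noncentral t. The stated 0.9996 is reproduced, so this simple calculation matches the plan's base case although the article mentions a linear mixed model.

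**Other scenarios.**

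| True difference | Stated | 35 per arm | 41 per arm |
|---|---|---|---|
| +7 | above 80% | 94.7% | 97.2% |
| +5 | above 95% | 84.6% | 89.7% |
| +2.5 | not printed | 60.8% | 67.7% |
| 0 | not printed | 31.9% | 36.4% |

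For d = 0: Φ(5/3.355 − 1.960) = Φ(−0.470) = 0.319, and Φ(5/3.100 − 1.960) = Φ(−0.347) = 0.364. With a noncentral t these are 31.2% and 35.7%.

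**The +5 figure.** Φ(10/3.355 − 1.960) = 0.846. At the same SDs, margin and n, power at +5 must lie below power at +7, which is 94.7% with 35 per arm. A one-sided 0.05 test gives 90.9% (35 per arm) or 94.3% (41 per arm), still short of 95%. A margin of 10 would give 99.4%, but would put the base case at essentially 1 (Φ(23/3.355 − 1.960)), not 0.9996.

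**Advantage needed for 80% power.** d = (1.960 + 0.842) × SE − 5: 2.80 × 3.355 − 5 = 4.4 points at 35 per arm; 2.80 × 3.100 − 5 = 3.7 points at 41 per arm.

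**Sensitivity to the SD** (assumed common SD s, 35 per arm, d = 0; SE = s × sqrt(2/35)): 55% at s = 10, 74% at s = 8, 29% at s = 15. Power reaches 80% only when s ≤ 5/2.80 × sqrt(35/2) ≈ 7.5.

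**Superiority** (lower 95% limit above 0, 35 per arm), Φ(d/SE − 1.960): 97.2% at +13, 55.0% at +7, 31.9% at +5.

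**The case against.** Sizing a non-inferiority trial on an assumed advantage is legitimate. The article bases its differences on earlier studies, including a randomized crossover trial for the +5, admits that data are limited, and lists small sample size as a limitation. Several simulations were run and not all need be printed. The SDs are described as maxima of measured LVEF, so the SD of change, or the residual SD in a mixed model, may be smaller. All this stands, and it means that 32% must be given with its SD range. It does not rescue the robustness claim: the shortfall at equality persists over assumed SDs of 8 to 15.

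A smaller SD could also produce the figure above 95% at +5: that needs s ≤ 10/(1.960 + 1.645) × sqrt(35/2) ≈ 11.6. The article gives no such SD for that scenario, and power at equality would then still be only Φ(5/2.77 − 1.960), about 44%.

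Three stronger readings are tempting and are not supported.

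- A reader might infer that a true CSP benefit could not be claimed. Superiority can be read from the same two-sided 95% interval once non-inferiority is shown, and the full protocol or analysis plan, neither of which is shown here, may already say so.
- A reader might infer that, with BVP at -1, CSP could be declared non-inferior with a mean change near -6. That confuses the margin with the decision rule. The lower limit must exceed -5, so the observed difference must exceed −5 + 1.960 × 3.355, about +1.6; with BVP at -1, CSP would need an observed mean of about +0.6.
- A reader might infer ample power for superiority in general. It is ample only at +13.

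**Conclusion.** The concern holds as a point about what the power paragraph shows and what the article states. On the article's own inputs, which reproduce its base-case power, the design has about 32% power at equality (36% if all 82 are evaluable) and needs CSP to be truly better by about 4.4 points (3.7 with 41 per arm) for 80%. The claimed robustness over a plausible range is therefore not shown, and the +5 scenario is overstated at the stated SDs: about 85% to 90%, not above 95%.

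The 32% rests on SDs of 13 and 15 applying to the change in LVEF; under assumed smaller SDs it is 55% (SD 10) or 74% (SD 8). Using non-inferiority as the sole stated aim is consistent across the article and is not itself an error. The missing superiority step is a gap in the article only; it may be filled elsewhere.

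**What to change.** 1. Restate the power paragraph. Add the zero-difference case (about 32% with 35 per arm, 36% with 41) with its range over the SD of change, correct the +5 figure to about 85% (90% with 41 per arm) or state the inputs that give more than 95%, and say that the sample size relies on CSP being better by about 4 to 5 points.
2. Before the primary analysis expected in 2026, state a fixed-sequence rule, or confirm it if the full protocol or analysis plan already has it: if the lower limit of the two-sided 95% interval for CSP minus BVP exceeds -5, conclude non-inferiority and then test superiority from the same interval (lower limit above 0).

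The cost is wording only. No patients are added, and the fixed sequence uses no extra alpha. The price of the first change is a less favourable robustness statement.

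### The power stated as over 95% for the +12%/+7% scenario is about 84–85% on the plan's own inputs

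*Protocol article*

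**What the plan says.** All the relevant statements are in the protocol article, under Sample size and statistical considerations.

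- **Test.** "The study is designed to test the two‐sided hypothesis", "at a type I error level of 0.05", with a non-inferiority margin of 5 LVEF points.
- **Variability.** "the maximum standard deviation of measured LVEF in the CSP group was 13% and 15% in the BVP group". The section then uses 13 and 15 as the SDs of the LVEF change.
- **Main scenario.** Mean changes of +"12% in the CSP group and −1% in the BVP group", with 35 patients per arm and power 0.9996.
- **Conservative scenario.** Means of +7 (CSP) and 0 (BVP), again with SDs 13 and 15: "the calculated power remains above 80" per cent.
- **Scenario from the randomized crossover trial.** "CSP mean ejection fraction change: +12%, BVP mean ejection fraction change: +7%), the calculated power would remain >95" per cent. Only the means are given here; no other SD, margin, alpha or sample size is printed.

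A separate sentence adds that "an allowable absolute difference of 5% in echo measurement of LVEF with Simpson biplane was set to cover the intraobserver variability". It does not say whether this allowance enters any power calculation.

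**The concern.** For a fixed n, SD, margin and alpha, non-inferiority power depends only on the true advantage plus the margin, and it falls as the advantage shrinks. The section gives a bound of 80% for a 7-point advantage and a bound of 95% for a smaller, 5-point advantage. That ordering suggests that at least one figure is wrong or that the scenarios used different inputs. The two figures may have been interchanged, or computed with different margins; the text does not allow one to tell.

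The scenario matters because the section concedes that robust estimates are lacking and takes its main assumption from a non-randomized study. The +12/+7 scenario is the only one drawn from a randomized comparison. A reader who sees over 95% will conclude that the trial is nearly certain to show non-inferiority even if the CSP advantage is only 5 points, and will misjudge how likely an inconclusive result was.

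**Working it through.** **Inputs, all from the sample size section:** SD 13 (CSP) and 15 (BVP); 35 evaluable per arm; margin 5; two-sided 0.05, so 0.025 in the non-inferiority tail (z = 1.960). For the +12/+7 scenario the SDs, n, margin and alpha are carried over, because nothing else is stated.

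**Formula.** Power = Φ((true difference + margin)/SE − 1.960), where SE = √((13² + 15²)/35) = √(394/35) = 3.355. Each result was also computed with the noncentral t (Welch) and by simulation of 100,000 trials.

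**Step 1: reproduce the plan's headline (+12 vs −1).** (13 + 5)/3.355 = 5.365; Φ(5.365 − 1.960) = 0.9997. The t calculation gives 0.99956, which rounds to the stated 0.9996. Other settings do not give 0.9996 by the t calculation:

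| Change to the inputs | Headline power |
|---|---|
| No margin | 0.968 |
| One-sided 0.05 | 0.9999 |
| 41 per arm | 0.9999 |
| Margin 10 (5 + 5) | 1.0000 |

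Among the settings tried, then, the headline matches only a margin of 5, two-sided 0.05 and 35 per arm.

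**Step 2: apply the same calculation to the other scenarios.**

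| Scenario | (Difference + margin)/SE | Normal | t | Simulation | Stated |
|---|---|---|---|---|---|
| +12 vs −1 | 18/3.355 = 5.365 | 0.9997 | 0.9996 | 0.9996 | 0.9996 |
| +7 vs 0 | 12/3.355 = 3.577 | 0.947 | 0.941 | 0.943 | above 80% |
| +12 vs +7 | 10/3.355 = 2.981 | 0.846 | 0.836 | 0.839 | over 95% |

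**Step 3: try more favourable readings of +12/+7.**

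| Reading | Normal | t |
|---|---|---|
| All 82 evaluable, 41 per arm (SE = √(394/41) = 3.100) | 0.897 | 0.890 |
| One-sided 0.05, 35 per arm | 0.909 | 0.904 |
| Both together | 0.943 | 0.940 |
| SD 13 in both arms, 35 per arm | 0.896 | – |
| Margin 10, 35 per arm | 0.994 | 0.993 |
| SD 13 in both arms, 41 per arm, one-sided 0.05 | 0.967 | – |

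Only the last two pass 95%. Margin 10 is incompatible with the 0.9996 headline. The last row drops the BVP SD, the dropout allowance and the two-sided alpha all at once.

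**Step 4: what 95% would require (normal formula).** The difference plus the margin must reach (1.960 + 1.645) × 3.355 = 12.09. With a 5-point advantage, that means a margin of about 7.1. Alternatively, it takes a common SD of at most about 11.6 with 35 per arm, or about 52 evaluable per arm with the stated SDs.

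**The case against.** Four points can be made for the plan.

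1. **Both figures are lower bounds.** A bound of 80% does not exclude 99%, so the two statements do not strictly contradict each other. This is correct, and the odd ordering is a warning sign rather than proof. The proof is the calculation: the 7-point scenario reaches only 94–95%, so on common inputs the 5-point scenario must lie below that. It also follows that a simple interchange would not fully repair the text, since over 95% is slightly too high for the 7-point scenario at 35 per arm.

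2. **The SDs are not restated for +12/+7.** A smaller, unstated SD of about 11.6 or less could yield 95%. That is a real caveat. But no such value is printed, the section describes 13 and 15 as the maximum observed, and it uses them in both other scenarios. If a different SD was used, the reader needs to be told.

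3. **The 5-point measurement allowance may have been added to the margin.** A total of 10 gives 0.993–0.994. The 0.9996 headline rules this out for the main scenario. It cannot show what was done in the later simulations, but scenarios run on different margins would themselves need correcting. The section also names a linear mixed model, but it states the distributions of the change directly, and the two-sample calculation on those reproduces the headline.

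4. **The practical consequence is limited.** Power remains above 80%; the 70 patients were derived from +12/−1, not from this scenario; and the crossover trial compared BVP with HBP, whereas LBBAP is preferred here. This stands, and it limits the finding to the claimed robustness.

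**Conclusion.** The stated power of over 95% for "CSP mean ejection fraction change: +12%, BVP mean ejection fraction change: +7" per cent is wrong on the plan's own inputs. The value is about 84–85% (0.846 normal, 0.836 t), at least 10 percentage points lower. The type II error is about 15–16% (1 − 0.846 = 0.154; 1 − 0.836 = 0.164), roughly three times the maximum implied by the text.

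This rests on carrying the SDs of 13 and 15, the 5-point margin, two-sided 0.05 and 35 per arm over to this scenario. The stated headline supports the margin, alpha and n, and no other SDs are given. The finding does not show that the trial is underpowered by the usual 80% standard. It shows that the claimed robustness is overstated in the one scenario based on randomized data.

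**What to change.** Restate the three figures on one basis (35 evaluable per arm, SDs 13 and 15, margin 5, one-sided 0.025, equivalent to two-sided 0.05):

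- +12 vs −1: 0.9996
- +7 vs 0: about 0.94–0.95
- +12 vs +7: about 0.84–0.85

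Say explicitly that all three use the same margin, alpha and n. If the figure of over 95% came from a different SD, margin or sample size, state those inputs and justify the difference from the headline calculation. In either case, make clear that the 5-point measurement allowance is not added to the margin in the headline power.

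The cost is a one-sentence correction. The quoted power becomes less favourable but stays above 80%, and no extra patients or design changes are needed.
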